## Abstract

**Purpose:**

There is increasing demand for colorectal cancer (CRC) surveillance, but healthcare capacity is limited. The burden on colonoscopy resources could be reduced by personalizing surveillance frequency using the fecal immunochemical test (FIT). This study will determine the safety, cost-effectiveness, and patient acceptance of using FIT to extend surveillance colonoscopy intervals for individuals at elevated risk of CRC.

**Methods:**

This multicenter, prospective, randomized controlled trial will invite participants who are scheduled for surveillance colonoscopy (due to a personal history of adenomas or a family history of CRC) and who have returned a low fecal hemoglobin (< 2 μg Hb/g feces; F-Hb) using a two-sample FIT (OC Sensor, Eiken Chemical Company) in the prior 3 years. A total of 1344 individuals will be randomized to either surveillance colonoscopy as scheduled or delayed by 1 or 2 years for individuals originally recommended a 3- or 5-year surveillance interval, respectively. The primary endpoint is incidence of advanced neoplasia (advanced adenoma and/or CRC). Secondary endpoints include cost-effectiveness and consumer acceptability of extending surveillance intervals, determined using surveys and discrete choice experiments.

**Conclusion:**

This study will establish the safety, cost-effectiveness, and acceptability of utilizing a low FIT Hb result to extend colonoscopy surveillance intervals in a cohort at elevated risk for CRC. This personalized approach to CRC surveillance will lead to a reduction in unnecessary colonoscopies, increases in healthcare savings, and a better patient experience.

**Trial registration:**

Registration was approved on December 9, 2019 with the Australian New Zealand Clinical Trials Registry ANZCTR 12619001743156.

## Introduction

Colorectal cancer (CRC) is the third most common non-cutaneous solid cancer worldwide accounting for 1.9 million newly diagnosed cases in 2020 and is the second leading cause of cancer related death, with almost 1 million deaths reported in 2020 [1]. These numbers are only set to rise, with an estimated 3.2 million cases of CRC globally in the year 2040 [2]. In the USA alone, CRC is estimated to rise from approximately 150–160,000 cases in 2020 to between 180 and 210,000 cases by 2040 [2, 3]. It has been well established that early detection and removal of colorectal neoplasia, including CRC and pre-cursor lesions called adenomatous polyps (adenomas), can prevent many deaths [4], and colonoscopy is considered the gold standard for detection and/or removal of such lesions. Following the diagnosis of colorectal neoplasia, ongoing regular surveillance colonoscopy is recommended. However, with expected large increases in the rates of CRC diagnoses, the workload demand on hospitals to perform the associated increase in surveillance colonoscopies will only become more cumbersome in what are already strained health care systems [5]. Additionally, although uncommon, the procedure carries an element of risk to the patient, with adverse events from anesthesia, bleeding or perforation [6]. Most importantly, over 85% of individuals at elevated risk of CRC undergoing surveillance colonoscopy due to prior neoplasia or a family history of CRC have no significant findings [7], demonstrating the potential overutilization of colonoscopy in this population. There is clearly a need to identify those individuals who do not need such intensive colonoscopy surveillance.

Screening using the non-invasive fecal immunochemical occult blood tests (FITs) for detection of fecal hemoglobin (F-Hb) shed from neoplastic lesions, with colonoscopy follow-up for those testing positive, can effectively reduce CRC incidence, severity, and mortality. This is through diagnosing cancers earlier and by detecting and removing the pre-cursor lesions [8]. FIT has a good sensitivity for detection of CRC at 65–87% [9], and the concentration of Hb in the feces is positively associated with risk of advanced neoplasia (advanced adenoma or CRC) [10]. This association has also been observed in individuals with Hb concentrations below the positivity threshold. In the Dutch national screening program, the risk of advanced neoplasia was significantly higher for individuals with fecal Hb concentrations just below the positivity threshold, compared to those returning a fecal Hb of 0 µg Hb/g feces [11]. This was also supported in their follow-up findings that analyzed multiple rounds of screening, where individuals with undetectable and low (< 2 µg Hb/g feces) concentrations of Hb in the feces had the lowest risk for advanced neoplasia [12]. Although these studies were performed in an average risk screening population, the FIT sensitivity for CRC in an elevated risk population is 80% with a specificity of 89% [13]. Taken together, these data suggest that fecal Hb concentrations from FIT completed before surveillance colonoscopy could be a suitable tool to inform postponement of colonoscopies in those who return a very low fecal Hb concentration, thereby reducing the demand on colonoscopy resources.

Optimizing surveillance colonoscopy frequency is challenging, evident by the changing guidelines implemented in Australia for CRC prevention in recent years [14, 15], as well as the different recommendations around the world [16, 17]. While there are studies supporting the benefits of CRC screening [18, 19], the benefits and cost-effectiveness of surveillance colonoscopy are less clear [7], due to limited prospective data. A study using simulation models in the USA suggested that a 10-year colonoscopy interval was more cost-effective than a 5-year interval, whereas an intensive surveillance of 3-yearly intervals was more harmful and resulted in reduced quality-adjusted life years [20]. It may be possible to guide optimal surveillance intervals using quantitative FIT, to balance cancer prevention and overutilization of colonoscopy procedures. When modelling surveillance strategies to compare annual FIT to 5-yearly colonoscopy, FIT was deemed to be as effective and less costly than colonoscopy; it reduced the number of colonoscopies by 45% and was associated with a lower rate of complications [21]. Personalizing surveillance based on FIT Hb concentration would lead to a reduction in the number of colonoscopies. Determining the cost savings of extending surveillance intervals in this context is now needed to justify such changes to clinical care.

Any changes to clinical policy that involves a change to the interval between colonoscopies based on FIT Hb concentration could result in distress amongst consumers. Participants may experience reservations about the efficacy of FIT in detecting abnormalities (i.e., lower response efficacy for FIT than colonoscopy) and have, as a result, greater anxiety and fear of cancer, resulting in decreased quality of life [22]. Alternatively, it may be the colonoscopy procedure itself causing distress. Preference for different surveillance strategies is likely to be, at least in part, dependent on perceived or anticipated participant burden, which influences uptake in CRC screening programs [23]. Perceived inconvenience is a significant predictor of compliance with healthcare recommendations, particularly among some under-served groups in the population [24]. It is therefore possible that individuals at increased risk for CRC will accept changes to surveillance strategies if they perceive the change to be less onerous and as effective. This could also be related to health activation, which describes the skills, confidence, and knowledge a person has in managing their own health [25]. Recent small studies have explored participants’ responses to a possible change to the surveillance process. Participants varied in level of CRC risk but, regardless of risk level, it was reported that an annual FIT was preferred over three yearly colonoscopies in those with no experience of surveillance [26, 27]. Conversely, those with a surveillance history believed that colonoscopy would be more accurate than FIT [26]. This suggests differences in either perceived response efficacy for the two approaches, or a reluctance to change usual practice, or both. It is therefore important to evaluate participant response to actual change in surveillance practice.

The use of FIT Hb concentrations could be a simple and effective way to personalize surveillance colonoscopy frequency. To our knowledge, there have been no randomized controlled trials (RCT) to determine if colonoscopy surveillance intervals can be safely extended in elevated risk CRC surveillance cohorts based on prior low FIT Hb concentration. Based on this, we have designed a randomized controlled trial in a cohort of individuals undergoing regular surveillance colonoscopy, to assess the safety, acceptance, and cost-effectiveness of extending the frequency of colonoscopy based on FIT Hb concentration.

## Objective

This randomized controlled trial will determine if it is safe to delay surveillance colonoscopy procedures by 1 to 2 years in patients with an elevated risk for CRC who have low FIT Hb levels and are undergoing surveillance colonoscopy with a 3- or 5-year surveillance interval. It will also determine the cost savings of delaying colonoscopy procedures, as well as the level of consumer acceptability if such changes were implemented into standard clinical care.

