Two-sample OC-Sensor FIT kits (Eiken Chemical Company, Tokyo, Japan) will be sent annually only to participants who are enrolled into the intervention arm, on their original guideline scheduled surveillance colonoscopy due date. Participants on a 5-year surveillance and with a 2-year delay will receive two FIT kits (1 each year). Participants on a 3-year surveillance will receive one FIT. The colonoscopy procedure will be performed on-time (control group — no FIT required) or on the delayed due date (Intervention group) if the interval FIT is negative (i.e., < 20 µg Hb/g feces). Any participants presenting with symptoms will be scheduled for colonoscopy as soon as possible regardless of trial intervention and will be withdrawn from the study. At the completion of the study and collection of all data, analysis will be performed to determine the primary and secondary outcomes.

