### Outcome parameters (endpoints)

Primary outcome:Incidence of advanced neoplasia (advanced adenoma or CRC) in the control and intervention groups.

Secondary outcomes:Incidence of complications from colonoscopy (admissions for bleeding or perforation, or death).Risk factors associated with advanced neoplasia including age, sex, family history of CRC, previous history of adenoma, number of prior colonoscopies.Cost-effectiveness of a modified surveillance frequency using interval FIT compared to standard surveillance practice.Acceptability to consumers of changes to the surveillance strategies and the variables that predict this attitude.

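### The objective and conclusion describe delay on a low FIT, but the randomized strategy is delay conditional on negative interval FITs, and the analysis section calls the mandated FIT-triggered colonoscopy non-adherence

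*Protocol article*

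**What the plan says.** Several parts of the protocol article state the safety question without interval testing:

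- **Objective:** the aim is to "determine if it is safe to delay surveillance colonoscopy procedures by 1 to 2 years in patients with an elevated risk for CRC who have" a low FIT result.
- **Introduction:** the evidence gap is whether intervals can be "safely extended in elevated risk CRC surveillance cohorts based on prior low FIT Hb concentration".
- **Abstract, Conclusion:** "This study will establish the safety, cost-effectiveness, and acceptability of utilizing a low FIT Hb result to extend colonoscopy surveillance intervals".
- **Enrolment criteria:** the intervention is defined only as lengthening the interval, from 3 to 4 years or from 5 to 7.

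The conduct sections describe something more:

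- **Study schedule:** FIT kits "will be sent annually only to participants who are enrolled into the intervention arm, on their original guideline scheduled surveillance colonoscopy due date". Table 1 places one FIT at month 0 in the 3-year stratum, and FITs at months 0 and 12 in the 5-year stratum. The delayed date applies if the interval FIT is below 20 µg Hb/g. For the on-time arm the text notes "control group — no FIT required".
- **Interval FIT Hb analysis:** a positive FIT cancels the delayed date, colonoscopy is arranged as soon as possible, and the participant stays enrolled.

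Among the endpoints, interval FIT is named only in a secondary one: "Cost-effectiveness of a modified surveillance frequency using interval FIT compared to standard surveillance practice". Under Statistical analyses (Advanced neoplasia incidence), a colonoscopy moved forward because of a positive FIT is an example of non-adherence. It is to be handled by per-protocol, modified intention-to-treat or as-treated analyses beside the primary intention-to-treat analysis.

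**The concern.** The arms differ by a package: a longer interval, plus one or two further FITs that can end the delay. If advanced neoplasia proves similar in the two arms, the result supports the package. It does not show how much is owed to the low FIT at entry and how much to the later FITs picking out people who should not wait.

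This matters because the article expects its results to inform national guidelines. Its limitations paragraph also contemplates carrying the strategy over to people who have colonoscopy only. A reader who takes the objective and conclusion at face value could extend intervals without the interval testing under which the evidence was gathered.

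The ambiguity also reaches the analysis. If the strategy is delay with FIT, a participant who tests positive and has an early colonoscopy has adhered. If it is delay alone, that participant has not. The article writes the procedure the first way and labels it the second way, so the per-protocol and as-treated populations rest on an unsettled definition.

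**Working it through.** **The plan's own figure.** The point does not rest on the sample size, but the check shows that nothing in it needs to move. For 9% versus 14%, two-sided alpha 0.05, 80% power and pooled variance:

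n = [1.960·√(2·0.115·0.885) + 0.842·√(0.09·0.91 + 0.14·0.86)]² / 0.05² = 638 per group.

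Inflating by the 5% poor-preparation rate in the Colonoscopy procedure section gives 638/0.95 = 672, the stated number. The article does not say that this is how it was reached. Its 5-point difference is described as one between the groups, which fits the arms as randomized.

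**The two descriptions side by side.**

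| Element | Objective, abstract conclusion | Study schedule, Interval FIT Hb analysis |
|---|---|---|
| Basis for delay | low FIT at or before entry | low FIT at entry and negative interval FIT(s) |
| Testing during the delay | not mentioned | 1 FIT (3-year) or 2 FITs (5-year) |
| After a positive FIT | not mentioned | delay ends, colonoscopy as soon as possible |
| Status of that colonoscopy | not addressed | required, participant stays enrolled; but non-adherence under Statistical analyses |

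**How often interval FIT could end the delay.** With positivity q per round and independent rounds, the share brought forward is q in the 3-year stratum and 1 − (1 − q)² in the 5-year stratum.

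| q | 3-year | 5-year |
|---|---|---|
| 2% | 2% | 4.0% |
| 5% | 5% | 9.8% |
| 11% | 11% | 20.8% |

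The 11% is 1 − 0.89, from the specificity for CRC in elevated-risk people cited in the Introduction. It is used only as an upper-end assumption: no threshold is given there, and trial participants are selected for Hb below 2 µg/g, so their rate should be lower. The 2% and 5% are assumed. Of 672 intervention participants, the extremes are 0.02 × 672 ≈ 13 (all 3-year, lowest q) and 0.208 × 672 ≈ 140 (all 5-year, highest q).

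**What the non-adherence label does.** Let f be the share brought forward by FIT, y the advanced neoplasia rate in them, and r the rate in those who wait. The intention-to-treat rate in the intervention arm is f·y + (1 − f)·r. A per-protocol analysis that drops the FIT-positives reports r, which is lower by f·(y − r). The Introduction says that higher fecal Hb goes with higher risk of advanced neoplasia, so y > r is expected and the exclusion would tend to make delay look safer. An as-treated analysis that moves these participants to the on-time group removes them from the delayed group in the same way, and adds a flagged group to the comparator. The article gives no y for this population, so the shift cannot be computed.

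**The case against.** The best reply is that the wording is shorthand. Interval FIT has its own Methods heading and columns in Table 1. The abstract's purpose speaks broadly of using FIT to extend intervals, and the cost analysis models FIT within a surveillance program. Nowhere does the article say that a prior low FIT alone is enough. Participants also come from a program that already offers FIT every 1 to 2 years, so testing during a longer interval continues its practice. This reply stands far enough to rule out the harsher reading. A reader might infer that the trial cannot support its stated claim at all, but the documents do not bear that out: a low FIT is the entry condition, and intention-to-treat validly tests the whole strategy against standard care.

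A second tempting reading is that leaving controls without FIT is a flaw. It is not. Controls have colonoscopy at month 0, when the first interval FIT is sent, so they have no delay to monitor.

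A third is that early colonoscopies cost power. That requires the 5-point difference to belong to an uninterrupted delay, which the Sample size section does not say.

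Finally, the statistical section does foresee brought-forward colonoscopies. But it does so by calling a required step non-adherence, and this is why shorthand is not a full answer: the mismatch passes from the wording into the planned analyses.

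**Conclusion.** The point holds as a mismatch between the stated question and the strategy tested, and it should be corrected before the analyses are run. The design and the primary intention-to-treat comparison are sound for delay with interval FIT and colonoscopy if positive, against on-time colonoscopy. They do not isolate delay on the earlier low FIT without interval testing, and the objective and conclusion should not read as though they did.

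The mismatch exists at any positivity rate. Its practical weight depends on how many participants are brought forward, roughly 2% to 21% across strata under the assumptions above, and on what is found in them, which the article does not predict. No change to the arms, sample size or clinical management follows.

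**What to change.** 1. State the primary objective, the primary contrast and the conclusion as: surveillance interval extended by 1 or 2 years with interval FIT, and colonoscopy if positive, versus on-time colonoscopy. Limit the safety claim to that strategy.
2. Reconcile the Objective, the abstract Conclusion, the Study schedule, the Interval FIT Hb analysis section and the Statistical analyses section, so that colonoscopy triggered by a positive interval FIT counts as following the assigned strategy in the per-protocol and as-treated analyses.
3. As a companion to the restated claim, report descriptively for each stratum the share of the intervention arm brought forward by FIT, and the advanced neoplasia found by each route (FIT-triggered or at the delayed date). Readers can then see how much of the safety result rests on the added testing.

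The cost is some rewording, one definition in the analysis text and one descriptive table from data already collected. The real price is a narrower claim: the trial would no longer read as evidence for extending intervals without interval FIT.

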## Methods and design

### Trial design

This study will be a multicenter, randomized controlled trial at public and private sector hospitals across the southern region of South Australia including Flinders Medical Centre, Noarlunga Hospital, Flinders Private Hospital, and the Tennyson Centre Day Hospital. Invitees will be those at elevated risk for CRC who are enrolled in the Southern Cooperative Program for the Prevention of Colorectal Cancer (SCOOP) program [28, 29] and who are due for surveillance colonoscopy at one of the study sites (Fig. 1). The SCOOP program was established in South Australia in 1999 [29], with the purpose of improving adherence to the Australian National Health and Medical Research council guidelines [15] for frequency of colonoscopy surveillance of individuals with an elevated risk of CRC. Individuals who are eligible for the SCOOP program are those at increased risk of CRC due to any one of the following criteria: (1) a personal history of colonic neoplasia (adenoma, sessile serrated lesion and/or CRC), (2) a family history of a primary degree relative with CRC diagnosed under the age of 55, and/or (3) two primary degree relatives or one primary and one secondary degree relative with CRC diagnosed at any age. As part of the SCOOP, research program individuals are provided with FIT in the interval between their 3- or 5-yearly surveillance colonoscopies [30, 31] at intervals of every 1–2 years. The FIT is offered beginning 1 year after their colonoscopy and 2 years prior to their subsequent scheduled surveillance colonoscopy when on a 5-year surveillance interval.

**Fig. 1 Fig1:**
[figure not shown]
Trial design. Flow chart of participant selection, recruitment, randomization arms, survey participation, and study endpoints. FIT, fecal immunochemical test; Hb, hemoglobin; CRC, colorectal cancer; QOL, quality of life; DCE, discrete choice experiment

### Enrolment criteria

Inclusion criteria for enrolment into the study include:Males and females enrolled in the SCOOP surveillance colonoscopy program.Aged older than 18 years of age.Individuals who have either had a previous colonoscopy finding of adenoma, or who have a significant family history of CRC [32].Individuals due for surveillance colonoscopy within the next 6 months after a recommended interval of three or five years.Individuals with a low FIT Hb concentration (< 2 μg Hb/g feces) within the last 3 years of their next scheduled colonoscopy.

Exclusion criteria encompass the following:Individuals with a familial syndrome of CRC or inflammatory bowel disease (IBD).Individuals with a personal history of CRC or sessile serrated lesions.Individuals scheduled for colonoscopy for any indication other than surveillance.Inability to understand study information and give informed consent.

Endoscopist exclusion criteria for this study will be:Not listed as an investigator on the study (for private sector hospital endoscopists).Not performing colonoscopy at a participating hospital.

Individuals with a low FIT Hb result (i.e., < 2 µg of Hb per g of feces) which was completed up to 3 years before their scheduled colonoscopy will be stratified for current colonoscopy interval (i.e., 3 or 5 years). Each group will be randomly assigned (1:1) to intervention or control. Intervention will extend surveillance colonoscopy interval by approximately one third:If guideline sets a 3-year surveillance interval (as usually recommended following an advanced adenoma [32]), the interval will be extended to 4 years.If guideline sets a 5-year surveillance interval (as usually recommended following a non-advanced adenoma or no neoplasia [32]), the interval will be extended to 7 years.

An interval is considered to have been appropriate if done within 6 months of the set time [33, 34].

Randomization will be performed using the stratified method with block randomization, controlling for (1) the referring endoscopic specialist, (2) the participating private or public hospital, and (3) the recommended surveillance interval. Participants and referring endoscopists will not be blinded to the randomization arm. Those not randomized to the Intervention group will receive standard clinical care, following the Australian National Health and Medical Research Council (NHMRC) guidelines for colonoscopy surveillance intervals [32].

